The limited waiver will apply only to MSKCC. Any participating sites that require a limited waiver must obtain it from their own local IRB/Privacy Board (PB) via a separate protocol addendum or request. It is the responsibility of the MSKCC staff to confirm the participating data collection sites(s) have a limited waiver approved by their local IRB(s)/PB(s).

All patients meeting the eligibility requirements will be considered for enrollment regardless of sex, race, or religion. Eligibility criteria may not be waived by the investigator. Discussions regarding protocol enrollment and patient eligibility may begin with any of the investigators named on the protocol or their associates. Patients will be made aware of the protocol, its specific aims and objectives, and the potential risks and benefits that the patient may incur. Patients will be required to read, agree to, and sign an IRB-approved Informed Consent form prior to registration. There will be no financial compensation for patients enrolling in this protocol. Over 120 new patients with stage II or III rectal cancer are treated at MSKCC every year.

The study will be opened at other high-volume rectal cancer centers. The investigators from those institutions have embraced the concepts of TNT and NOM, and demonstrated their ability to accrue, having enrolled over 270 patients to the TIMING trial (PI: [name]). Many of these investigators also accrued to the ACOSOG Z6041 trial (PI: [name]) investigating the efficacy of CRT and local excision in patients with T2N0 rectal cancer.[89] It is expected that approximately 87 patients will be recruited at MSKCC and the remaining 238 will be recruited at the outside centers. Accrual rates are expected to vary across sites based on location and available staff support. Patients will be screened and enrolled at the participating sites. It is recommended that patients have all of their treatment at the primary enrolling site. However, they may receive some of their treatment at affiliated sites. An affiliated site is defined as one that is under the IRB of the enrolling institution.

Please refer to Section 15.0, Research Participant Registration and Randomization Procedures, for details on enrollment procedures.

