## 14.0 BIOSTATISTICS

**14.1 Primary objective:** *To evaluate 3-year DFS survival in patients managed with TNT and TME or NOM, compared with standard historical controls managed according to standard of care (CRT and TME followed by ACT).*

We hypothesize that 85% of patients with LARC treated with TNT and selective NOM will be alive and free of disease at 3 years. The 3-year DFS for similar patients (stage II/III LARC within 6 cm from the anal verge) treated according to the standard of care (CRT, TME, and ACT) is 75%. (Survival data provided by Maas et al from a pooled analysis of 3105 rectal cancer patients treated with CRT and TME). [35] In this trial, each arm is designed as a single-stage study that discriminates between 3-year DFS rates of 75% (historical control) and 85% (Study Arms, INCT and CNCT). No formal statistical comparison of the two arms is planned.

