For our power calculation, we assume uniform accrual over time and an exponential distribution for time to death. Based on our previous experience, we can assume that we will be able to accrue 2-4 patients per arm per month. Using the approach proposed by Lawless (1982), for 86% power, a two-sided type I error of 5% we will require 101 patients per arm. Based on our estimated accrual rate, a total of 202 patients can be accrued over 40 months with an additional 3-year follow-up.[95] With a sample size of 101 patients (each arm), we will consider the treatment regimen of an arm worthy of further study if the 3-year DFS rate exceeds (based on parametric exponential estimate) .82 (the upper critical value). The 3-year rates will be estimated using parametric exponential estimates as well as on Kaplan-Meier estimates. Analysis of the primary endpoint will occur 3 years following the completion of accrual. We anticipate about 10% loss to follow-up (dropouts that occur before the entire regimen has been completed), and will recruit an additional 10 patients per arm to account for this. Patient accrual for the entire trial is expected to take 40 months, with approximately 6 patients (2-4 per arm) per month. We will update the analysis after we have completed follow-up. Accrual has been completed a year ahead of schedule. Preliminary results indicate that we may require additional patients to detect differences in organ preservation rates, one of the secondary aims of this study. Based on this new information, we plan to increase accrual to 325 patients. As accrual has been progressing faster than initially estimated, we expect that, with the proposed increase, accrual will still be completed within the initially proposed accrual period.

This trial could complete with 3 possible results: both arms are worthy of further study, one arm is worthy of further study, no arm is worthy of further design. In all three cases, all Aim 2 analyses will be performed. In the ambiguous case when both the INCT and CNCT arms are worthy of further study, we will use a pick-the-winner strategy based on the number of NOM patients. This is described in more detail in section 14.2.

**14.2 Secondary objective 1.:** *To compare outcomes in patients treated on the two arms of this study, with respect to rates of organ preservation, compliance with the neoadjuvant protocol, and major adverse events.*

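### The primary cut-off of .82, its 5% error and its 86% power belong to 101 patients per arm and were not restated when accrual rose to 325

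*Protocol*

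**What the plan says.** Section 14.1 treats each arm as a single-stage study that "discriminates between 3-year DFS rates of 75% (historical control) and 85% (Study Arms, INCT and CNCT"). The size calculation reads "for 86% power, a two-sided type I error of 5% we will require 101 patients per arm". Its assumptions are "we assume uniform accrual over time and an exponential distribution for time to death", and "a total of 202 patients can be accrued over 40 months with an additional 3-year follow-up". The primary analysis is placed 3 years after accrual ends.

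The decision rule opens with "With a sample size of 101 patients (each arm), we will consider the treatment regimen of an arm worthy of further study if" and then sets a threshold for DFS at 3 years. An arm passes when its estimate "exceeds (based on parametric exponential estimate) .82 (the upper critical value"). About 10% loss is expected, covered in the initial plan by 10 extra patients per arm (222 in total).

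Later in the same paragraph, because of the organ-preservation secondary aim, the protocol says "we plan to increase accrual to 325 patients", still within the planned accrual period. Section 7.0 carries the new total: "approximately 87 patients will be recruited at MSKCC and the remaining 238 will be recruited at the outside centers", which is 87 + 238 = 325. No cut-off, error rate or power for the primary test is given at the larger size.

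**The concern.** A critical value for a test against 75% moves towards 75% as the sample grows. A value computed for 101 per arm is therefore too high for about 162 per arm if the test is still meant to be two-sided 5%. The protocol would then give two answers for the same data: the stated test could exclude 75% while the stated rule declares the arm not worthy of further study.

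This is the verdict on each arm's primary endpoint. It also decides whether the comparison of arms by number of non-operative patients in section 14.2 is used, since that step applies only when both arms pass.

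**Working it through.** **Inputs (section 14.1).** Null S0 = .75; alternative S1 = .85; two-sided 5%, so 2.5% in the upper tail; exponential times; uniform accrual over A = 40 months; F = 36 months' further follow-up; 101 per arm; cut-off .82 on the exponential estimate; 10% loss; revised total 325.

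**Assumptions.** Equal allocation: 325/2 = 162.5, taken as 162. Lost patients are simply removed: 162 × 0.9 = 145.8, taken as 146. Because the protocol reports that initial accrual finished a year early, 40 − 12 = 28 months is used as a faster-accrual case.

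**Formulas.** Hazard λ = −ln(S)/36 per month. The estimate is exp(−36·d/T), with d events and T person-months. The probability that a patient has an event by the analysis is 1 − [exp(−λF) − exp(−λ(A+F))]/(λA).

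**Step 1: reproduce the stated design.**
- λ0 = 0.2877/36 = 0.00799. The event probability is 1 − (0.750 − 0.545)/0.320 = 0.358.
- At 101 per arm this gives 36.2 expected events at 75%, and 22.5 at 85%.
- Delta-method standard error at the null: S0·(−ln S0)/√d = 0.75 × 0.2877/√36.2 = 0.0359. Critical value: .75 + 1.96 × 0.0359 = .820.
- Simulation (100,000 trials) puts the 97.5th percentile under 75% at .818, with power 86.1% at 85%.

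So .82 and 86% are the figures for 101 per arm. A plain binomial calculation does not fit (.834, power 67%).

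**Step 2: same method at the enlarged size.** For 162 per arm, expected events at 75% are 162 × 0.358 = 58.0 and the standard error is 0.2158/√58.0 = 0.0283. The critical value is .75 + 1.96 × 0.0283 = .8055. The cut-off .82 lies 0.07/0.0283 = 2.47 standard errors above 75%, an upper tail of 0.67%. Simulation gives:

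| Analysed per arm | Accrual (months) | Error of .82 at 75% | Power of .82 at 85% | Cut-off for 2.5% upper tail | Power with that cut-off |
|---|---|---|---|---|---|
| 101 | 40 | 2.2% | 84.4% | .818 | 86.1% |
| 162 | 40 | 0.52% | 89.8% | .804 | 97.2% |
| 146 | 40 | 0.71% | 88.9% | .807 | 95.9% |
| 162 | 28 | 0.71% | 88.9% | .807 | 95.8% |
| 146 | 28 | 1.0% | 87.8% | .810 | 93.8% |

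Repeat simulations move the cut-offs by about .001.

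**Step 3: how often the two answers differ.** At 162 per arm with 40-month accrual, the estimate falls between about .804 and .82 in about 7% of trials at a true 85%, 19% at 83% and 24% at 82%. At a true 83%, an arm passes in 66% of trials under .82 and 86% under the matching cut-off.

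**The case against.** The strongest reply is that nothing promised is broken. Section 14.1 promises two-sided 5% error and 86% power at 85%. With .82 kept, error is below the limit and power is above the promise. That stands, and it is why this is not a must-fix.

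A second reply is that the protocol ties .82 expressly to 101 per arm and never says that it governs 325, so the rule for the enlarged trial is unstated rather than wrong. The statistical analysis plan, not shown here, may supply it. This is a fair reading. But .82 is the only primary cut-off in the protocol, and the paragraph that changes the size leaves it in place. Either reading needs the same amendment.

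A third reply is that lowering the cut-off is not neutral. The trial is unblinded, and the proportions selected for non-operative management (66% and 79%) have already been seen. At a true DFS of 80%, moving from .82 to .804 raises the chance that an arm passes from 22% to 45%. This also stands: keeping .82 as a declared stricter bar is a legitimate choice.

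A reader might infer that the extra patients add almost nothing to the primary aim. The figures contradict this: with .82 fixed, moving from 101 to 162 per arm cuts the error from about 2.2% to 0.5% and raises power at 85% from about 84% to 90%. The protocol in any case gives a secondary aim as the reason for the increase.

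**Conclusion.** The point holds as a should-fix. The only primary cut-off and its stated error and power describe a trial of 101 per arm. Carried to 146-162 per arm, .82 has an upper-tail error of about 0.5-1.0% and power of about 88-90% at 85%, against a matching two-sided 5% cut-off of about .804-.810.

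A reader might take 0.5% as the error of the rule. It holds only with equal arms, no loss and 40-month accrual, and the baseline at 101 per arm is already about 2.2% because the cut-off is rounded up to .82. A reader might also infer a raised risk of a false-positive arm or a loss of planned power. Neither occurs. The real defect is that the stated test and the stated rule disagree for estimates between the matching cut-off and .82. All figures rest on the protocol's exponential model and uniform accrual.

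**What to change.** Before DFS data are read, amend section 14.1 to state the rule for the number analysed per arm, on the exponential estimate already specified. Choose one of two forms and record the reason:

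1. Recompute the cut-off for two-sided 5%. With 40-month accrual this is about .804 at 162 per arm (power about 97% at 85%) or about .807 at 146 (about 96%). Use the actual accrual time and number analysed.
2. Expressly keep .82 as a stricter bar and restate its upper-tail error (about 0.5-1.0%) and power at 85% (about 88-90%).

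The deciding estimator should not be switched to Kaplan-Meier in order to rescue .82, because that would change the primary analysis mid-trial. The cost is one paragraph of wording, with no further patients or data.

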## **12.0 CRITERIA FOR THERAPEUTIC RESPONSE/OUTCOME ASSESSMENT**

The primary objective of this study, 3-year DFS, will be assessed on the basis of surveillance procto/sigmoidoscopy, physical examination, and follow-up radiologic scans. For patients who receive TME or NOM, follow-up scans will occur according to current NCCN guidelines for rectal cancer surveillance. Patients in the NOM group will be evaluated using rectal MRI and endoscopic exam (section 10). Patients in the NOM group who undergo subsequent TME will be followed according to current NCCN guidelines. 3-year DFS will be defined as the percentage of patients alive without recurrence of disease at 3 years measured from the date of randomization. Patients in the NOM protocol who develop relapse at the site of the primary tumor but undergo curative TME with negative resection margins will not be counted as having recurrence. However, any patients developing local recurrence after TME, performed either immediately after neoadjuvant therapy or after a period of NOM, will be counted as having recurrence. Scans will be reviewed at MSKCC to resolve any discrepancies in interpretation. Scans showing equivocal evidence of local recurrence will be evaluated with additional imaging as necessary. Biopsy confirmation of local recurrence will be indicated for the purposes of the protocol. Isolated elevation of CEA, in the absence of other evidence of recurrent disease, will not be considered indicative of either local or systemic relapse. Symptomatic evidence of local recurrence will be corroborated on the basis of imaging and/or physical examination. Distant recurrence will also be assessed using follow-up CT scans of the chest, abdomen and pelvis. The MSKCC radiologist will review scans to resolve any discrepancies in interpretation. Central radiology review at MSKCC will review all incoming images and reports, but will only submit feedback on cases in which scans must be repeated or, in the case of interval or re-staging evaluations, where progression is identified in disagreement with the site investigator's assessment. Scans with equivocal evidence of distant recurrence will be evaluated via additional imaging, as

necessary. Biopsy confirmation of distant recurrence will be indicated for the purposes of the protocol.

Adverse events associated with CT and RT-CT will be assessed using the standard criteria described in section 11.0.

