Based on previous data, we anticipate a 20% NOM in the INCT arm, and 35% in the CNCT arm, after 3 years. The proportion of patients initially entered in the NOM protocol will be higher, but some will later relapse and require TME. For this reason, we anticipate that the proportion of patients with NOM at 3 years will be close to the pCR rates observed in previous studies. We estimated that the 222 patients required for the primary aim would be sufficient to detect differences in organ preservation rates. Our preliminary results indicate that the proportions of patients selected for NOM based on tumor response after completion of neoadjuvant therapy are much greater than expected: 66% in one arm and 79% in the other. Although many of these patients may eventually experience tumor regrowth requiring total mesorectal excision, the proportions of patients with a preserved rectum 3 years after diagnosis are likely to be greater than the original estimates. Therefore, based on the new information, we plan to increase accrual to 325 patients. There is limited information regarding treatment compliance and adverse events in patients who have received more than 4 or 6 cycles of INCT or CTNT. Therefore, these secondary objectives are considered exploratory. If both arms meet the endpoint in primary objective, we plan to use NOM rate to determine the more promising regimen using a “pick the winner” strategy. We will calculate the number of patients treated with NOM who are alive and free of disease 3 years following the start of the study. We will require at least 20 NOM patients in each arm to employ the following strategy: If there is a difference of 5 NOM patients between arms, the arm with more NOM patients will be deemed the winner. With 101 patients in each arm, 20% NOM in patients treated with INCT and 30% in patients treated with CNCT, we will have an 83% probability of selecting CNCT, a 1% probability of selecting INCT, and a 16% probability of considering the study inconclusive.

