In addition, we will calculate therapy compliance using the following measures: the number of days RT was held, the number of RT delays of  $\geq 1$  week, the number of dose delays and the number of dose reductions in INCT and CNCT. We will also calculate the rate of select hematologic events (as outlined in 17.2), select non-hematologic events (as outlined in 16.0), and unexpected Grade 3 or higher non-hematologic adverse events and surgical complications in each treatment arm. Comparisons will be done using the Wilcoxon Rank Sum test or the Fisher’s Exact test.

**14.3 Secondary objective 2.:** *To measure patient-reported functional outcomes and QoL in patients with LARC treated with NCT, CRT and NOM, and compare these to patients treated with TME.*

The primary analyses for this aim will use data combined across both treatment arms; however, differences according to treatment will also be investigated. The primary endpoint will be QoL as measured one year from the end of TNT. Secondary endpoints will be bowel, sexual, and bladder function. While the subscales will be reported, the primary secondary endpoints will be the total scores on the BFI, FSFI and IIEF. With a total of 325 patients accrued, we expect that 129 patients will obtain complete clinical response and 196 will undergo TME. Approximately 15 to 30 patients initially treated with NOM are expected to cross over to TME at some point during follow-up. For the primary analyses, the NOM group will include these cross-overs on an intent-to-treat analysis. In secondary analysis, patients who eventually crossed over to receive surgery will be included in the TME group. We define this analysis as a comparison between TME vs. durable NOM. Durable NOM is defined as 3-year disease-free survival. We expect that 70% of patients will complete the QoL assessment at 1 year. This response rate takes into account refusals to complete the QoL

questionnaires, and the approximately 20% of patients who will develop distant disease or die before the 1-year time point. Thus, at 1 year we expect to have information on 94 TME patients and 62 NOM patients.

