#### **14.4 Correlative studies: objectives**

The correlatives studies will be conducted in patients accrued at MSKCC only. During the past five years, an average of 120 patients with stage II and III rectal cancer have been treated at MSKCC; 43 of them had tumors located within 6 cm from the anal verge, and are potentially eligible for the trial. We estimate that 20 patients (less than 50% of eligible patients) will be accrued to the trial every year, for a total of 80 patients over the 4-year accrual period. Assuming equal distribution between arms, we anticipate that 56 patients will ultimately be treated with TME and 24 with NOM.

Endpoints for each of the aims will be compared between patients treated with TME and patients treated with NOM. Endpoints for each of the aims are as follows:

*14.4.1 To investigate the diagnostic performance of conventional and diffusion-weighted magnetic resonance imaging (DW-MRI) in identifying patients with LARC treated with TNT, who may benefit from NOM.*

Measurements used for correlation include mrTRG in T2-w imaging, assessment of DW signal intensity (SI), mrΔvolume between baseline and post-TNT examinations in both T2-w and DW imaging, and changes in ADC, true diffusion (D), and perfusion fraction (f) between baseline and post-TNT DW-MRI. The outcome will be the proportion of patients treated successfully with NOM, meaning the patient is free of disease at the 3-year endpoint, plus patients with ypT0 after TME.

This will be the first study investigating the diagnostic performance of conventional and DW-MRI in LARC patients treated with TNT and NOM. Therefore, this aim will be considered exploratory.

DW-MRI will be done for all MSKCC patients. Participating sites may perform DW-MRI, but this is not required. If one exam for a patient is performed as DW-MRI, all subsequent exams for the patient should be done using the same technique. If performed, DW-MRI will be captured in the appropriate case report forms.

*14.4.2 To evaluate the feasibility of using circulating tumor DNA and miRNA profiles in plasma to monitor tumor response to TNT in rectal cancer patients treated in both protocol arms.*

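### The pick-the-winner count in 14.2 does not require that the rectum is still in place, so patients who had margin-negative salvage TME count as NOM successes

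*Protocol*

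**What the plan says.** **Winner rule (Protocol 14.2).** If both arms meet the primary endpoint, the count is "the number of patients treated with NOM who are alive and free of disease 3 years following the start of the study". At least 20 NOM patients per arm are required, and a difference of 5 decides the winner.

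**Disease-free status (12.0).** "3-year DFS will be defined as the percentage of patients alive without recurrence of disease at 3 years measured from the date of randomization". NOM patients who relapse at the primary site but "undergo curative TME with negative resection margins will not be counted as having recurrence".

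**What the NOM rate was meant to be (14.2).** "The proportion of patients initially entered in the NOM protocol will be higher, but some will later relapse and require TME". The section therefore expects the 3-year NOM proportion to lie close to historical pCR rates, and it later speaks of the rectum being preserved 3 years after diagnosis.

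**Durable NOM (14.3).** In the secondary quality-of-life analysis, "patients who eventually crossed over to receive surgery will be included in the TME group". That comparison is named TME versus durable NOM, and the next sentence reads "Durable NOM is defined as 3-year disease-free survival".

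**Correlative studies (14.4.1).** The outcome counts "patients treated successfully with NOM, meaning the patient is free of disease at the 3-year endpoint", plus patients with ypT0 after TME. Sections 14.4.2 to 14.4.4 set such patients against those with residual tumor after TME.

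**The concern.** The rule exists to pick the arm that preserves more rectums, but its count never says so. Disease-free status in 12.0 was built for the DFS endpoint, where a successful salvage operation is properly not an event. Carried into 14.2, the same convention turns a lost rectum into an organ-preservation success.

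Nor does the phrase about patients treated with NOM exclude operated patients. Section 4.1 speaks of NOM patients including those with later TME. The primary quality-of-life analysis in 14.3 keeps cross-overs in the NOM group. The stopping rule in 14.5 refers to NOM patients who need TME. An analyst using the protocol's own vocabulary would include them.

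At stake is which regimen is named the more promising. An arm that sends more patients into NOM and loses more of them to salvage surgery could be declared the winner for organ preservation.

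**Working it through.** **1. Reproduce the plan's figure.** Inputs from 14.2: 101 per arm, NOM rates 20% (INCT) and 30% (CNCT), an arm wins if it leads by at least 5. With X ~ Bin(101, 0.20) and Y ~ Bin(101, 0.30) independent:

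- P(Y − X ≥ 5) = 82.0% (stated 83%)
- P(X − Y ≥ 5) = 0.9% (stated 1%)
- inconclusive = 17.1% (stated 16%)

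The stated figures reproduce without imposing the 20-patient minimum. The rates used are on the net-of-TME scale, so a count without TME leaves this calculation unchanged.

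**2. Apply the literal wording to the same design.** Section 14.3 expects 15 to 30 cross-overs among 129 NOM patients: 15/129 = 11.6%, 30/129 = 23.3%. Assume the same share in both arms and every cross-over disease-free.

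- At 11.6%: 0.20/(1 − 0.116) = 22.6% and 0.30/(1 − 0.116) = 33.9%, giving 86.3% / 0.6% / 13.1%
- At 23.3%: 0.20/(1 − 0.233) = 26.1% and 0.30/(1 − 0.233) = 39.1%, giving 90.5% / 0.4% / 9.1%

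With equal salvage the literal count mainly makes a decision more likely; it does not redirect it.

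**3. Let salvage differ between arms.** From the protocol: 325 patients, about 162 per arm; preliminary NOM entry of 66% and 79% (14.2, arms not named); hypothesised 3-year DFS of 85% (14.1). Assumed here: the 85% applies to NOM entrants in both arms, all salvage is successful, and the salvage shares are as listed.

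Literal rate = entry × 0.85: 0.66 × 0.85 = 56.1% and 0.79 × 0.85 = 67.2%. Salvage does not enter this formula, so the higher-entry arm wins with 93.8% probability whatever the salvage share.

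Rate without TME = entry × 0.85 × (1 − salvage share):

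| Salvage, lower- vs higher-entry arm | Rates without TME | Higher-entry arm picked | Other arm picked | Inconclusive |
|---|---|---|---|---|
| 10% vs 10% | 50.5% vs 60.4% | 90.4% | 1.0% | 8.6% |
| 20% vs 20% | 44.9% vs 53.7% | 86.3% | 1.8% | 11.9% |
| 30% vs 30% | 39.3% vs 47.0% | 81.7% | 2.8% | 15.5% |
| 12% vs 23% | 49.4% vs 51.7% | 46.9% | 17.9% | 35.3% |
| 30% vs 40% | 39.3% vs 40.3% | 37.3% | 24.3% | 38.4% |
| 20% vs 40% | 44.9% vs 40.3% | 9.0% | 63.0% | 28.1% |
| 40% vs 30% | 33.7% vs 47.0% | 97.5% | 0.2% | 2.4% |

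The 12% vs 23% row puts the two ends of the protocol's own cross-over range in opposite arms.

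**4. Sections 14.3 and 14.4, side by side.** In 14.3 a salvaged patient goes to the TME group by the grouping sentence, yet meets durable NOM by the definition that follows it. In 14.4 a NOM patient with regrowth, tumor in the salvage specimen and no later recurrence is disease-free at 3 years and also has residual tumor after TME. That patient fits both comparison groups.

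**5. Time origin.** The winner count runs from the start of the study, the preserved-rectum sentence from diagnosis, and DFS in 12.0 from randomization.

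**The case against.** The best defence is that the intent is plain. Section 14.2 plans on a NOM rate reduced by later TME and speaks of a preserved rectum, and the stated probabilities are computed on that scale. On this view one sentence merely omits a condition. That stands as to intent, and it means the design figures need no correction. It does not cure the rule, because an analyst must apply the written count and the protocol elsewhere calls operated patients NOM patients.

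The size is also open to challenge. Reversal needs unequal salvage, and the protocol gives no arm-specific figure. With equal salvage the same arm usually wins, and with more salvage in the lower-entry arm its lead grows. This stands.

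Several stronger readings are tempting but not supported:

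- **Durable NOM contains operated patients.** The grouping sentence in 14.3 moves them to the TME group. What remains is a contradiction between adjacent sentences.
- **The count would be taken at study month 36, before the 40-month accrual ends.** The rule applies only after both arms meet the primary endpoint, which is analysed 3 years after accrual closes. The time origin is loose wording that needs aligning.
- **The 15 to 30 cross-overs dwarf the margin of 5.** They are a total over both arms, while the margin is a difference between arms. An even split contributes nothing to it.
- **The rule merely compares initial NOM entry.** It still removes deaths, distant recurrence, unsalvaged regrowth and recurrence after TME.

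**Conclusion.** The point holds for the winner rule as written. Read with 12.0, it counts patients who lost the rectum at margin-negative salvage TME, contrary to the objective and to the scale on which the rule was planned.

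The effect runs from small to decisive. Against 94% under the literal count, a count without TME picks the higher-entry arm with 90% to 82% probability at equal salvage of 10% to 30%, 47% at 12% vs 23%, and 9% at 20% vs 40%. These figures rest on assumed salvage shares, an assumed 85% disease-free among NOM entrants in both arms, and preliminary NOM entry rates. They show what the wording can do and do not forecast the result.

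In 14.3 the defect is a contradiction to reconcile. In 14.4 it is an overlap between groups in aims declared exploratory.

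A reader might infer that the trial's main conclusion is at risk. It is not: the rule is conditional and sits in a secondary objective, no formal comparison of the arms is planned, and the primary DFS endpoint is untouched. The correction is worth making before the rule is applied, but it is not critical to the trial.

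**What to change.** Use one definition of durable NOM, or NOM success, in 14.2, 14.3 and 14.4: the patient entered NOM after TNT, is alive, has had no TME, and has had no local regrowth or distant recurrence at 3 years from that patient's own randomization. State that cross-overs to TME count as organ-preservation failures. Then:

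- **14.2:** replace the present count with this one, and drop the start-of-study and diagnosis origins.
- **14.3:** replace the sentence equating durable NOM with 3-year DFS, so that it agrees with the grouping rule before it. The intent-to-treat primary quality-of-life analysis can stay as it is.
- **14.4:** apply the same definition, so that a salvaged patient with tumor in the specimen falls only in the residual-tumor group.
- **12.0:** leave the DFS definition alone.

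The cost is wording. Surgery and recurrence are already recorded, and treatment and sample size do not change. The reported NOM success count will be lower than under the literal text.
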